## Abstract

**Background:**

Delirium is a frequent disorder in intensive care unit (ICU) patients with serious consequences. Therefore, preventive treatment for delirium may be beneficial. Worldwide, haloperidol is the first choice for pharmacological treatment of delirious patients. In daily clinical practice, a lower dose is sometimes used as prophylaxis. Some studies have shown the beneficial effects of prophylactic haloperidol on delirium incidence as well as on mortality, but evidence for effectiveness in ICU patients is limited. The primary objective of our study is to determine the effect of haloperidol prophylaxis on 28-day survival. Secondary objectives include the incidence of delirium and delirium-related outcome and the side effects of haloperidol prophylaxis.

**Methods:**

This will be a multicenter three-armed randomized, double-blind, placebo-controlled, prophylactic intervention study in critically ill patients. We will include consecutive non-neurological ICU patients, aged ≥18 years with an expected ICU length of stay >1 day. To be able to demonstrate a 15% increase in 28-day survival time with a power of 80% and alpha of 0.05 in both intervention groups, a total of 2,145 patients will be randomized; 715 in each group. The anticipated mortality rate in the placebo group is 12%. The intervention groups will receive prophylactic treatment with intravenous haloperidol 1 mg/q8h or 2 mg/q8h, and patients in the control group will receive placebo (sodium chloride 0.9%), both for a maximum period of 28-days. In patients who develop delirium, study medication will be stopped and patients will subsequently receive open label treatment with a higher (therapeutic) dose of haloperidol. We will use descriptive summary statistics as well as Cox proportional hazard regression analyses, adjusted for covariates.

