### Objectives

Definitions of variables in objectives are reported in Table 1.

**Table 1 T1:** Definition of study objectives

**Objective**	**Definition**
*Survival days in 28 days*	Number of days that patients survive in 28 days. All patients will be classified as either ‘alive at study day 28’ or, if dead, ‘dead at study day 28’ on an intention-to-treat basis.
*Delirium diagnosis*	Patients are diagnosed as delirious when they have at least one positive CAM-ICU screening during their complete ICU stay. Patients who were not delirious during their ICU-stay are considered as non-delirious patients.
*Delirium-and-coma-free days in 28 days*	Number of days that the patient is alive and not delirious and not in coma over 28 days starting from the day of inclusion. A delirium-and-coma-free day is defined as a negative CAM-ICU screening with a Richmond Agitation Sedation Score (RASS) greater than (more alert than) -3/-4/-5 during a day. In case a delirious patient is discharged to the ward, a delirium-free day is defined as a delirium observation scale score [30] of less than 3 during a complete day.
*Duration of mechanical ventilation*	Time in days that the patient is on the mechanical ventilator. If the patient is ventilated mechanically several times during one ICU admission, then the ventilator times are added. Both invasive and non-invasive ventilation will be registered. Ventilator-free days (in 28 days) will be calculated.
*Incidence of re-intubation*	Patients who need to be intubated within 28 days from randomization, following a previous extubation, irrespective of the reason for re-intubation, are counted as incident case for re-intubation.
*Incidence of ICU readmission*	Patients who need to be readmitted to the ICU during within 28 days from randomization, irrespective of the reason for readmission, are counted as incident cases for ICU readmission.
*Side effects*	Drowsiness, agitation, QTc-time prolongation (using 12-leads ECG or monitor strip with Bazett’s formula) and development of extra pyramidal symptoms such as tandem gait, dystonia, tremor, myoclonus, tics, rigidity, akathisia [31], determined daily by physical examination by the intensivist.
*Serious adverse event*	Any untoward medical occurrence or effect at any dose that results in one of the following outcomes and is not classified as a clinical outcome of delirium or the underlying disease using the description above:

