### Sample size calculation and statistics

Sample size calculation is based on the difference in survival from our previous prophylactic haloperidol study [19]. In this study, the median survival time in the control group was 18 days. If the true hazard ratio of control patients relative to intervention patients is 0.85, taking into account an accrual time of 90 days with 28 days of follow-up, we will need to study 647 patients per intervention group and 647 control patients to be able to reject the null hypothesis that the experimental and control survival curves are equal with probability (power) 0.80. The Type I error probability associated with this null hypothesis test is 0.05. Taking into account a dropout percentage of 10%, we will include 715 patients per group (Figure 1). A fixed sequence procedure will be followed. First, the highest dosage of prophylactic haloperidol will be compared with placebo using alpha 0.05 (two-sided). Only if H_0_ is rejected, subsequently the lower dosage of prophylactic haloperidol will be compared with placebo. Cox regression analysis will be used to test differences on 28-day survival in the intervention group compared with the placebo group.

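### The abstract's detectable effect, a 15% gain in survival time over 28 days, cannot occur at 12% placebo mortality and is not the hazard ratio of 0.85 from which the sample size was derived

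*Protocol article*

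**What the plan says.** The abstract (Methods) gives the design target: "To be able to demonstrate a 15% increase in 28-day survival time with a power of 80" per cent, with 715 patients in each of three groups. The next sentence adds: "The anticipated mortality rate in the placebo group is 12" per cent. No time point is attached to that mortality.

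Table 1, under Objectives, defines the survival measure: "Number of days that patients survive in 28 days". Table 2 lists 28-day mortality as the primary endpoint and 90-day mortality as secondary. The primary objective is to determine the effect of prophylactic haloperidol on 28-day survival and sets no threshold.

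The section Sample size calculation and statistics uses different inputs. From the earlier prophylaxis study it takes that "the median survival time in the control group was 18 days". The effect is a hazard ratio: "If the true hazard ratio of control patients relative to intervention patients is 0.85". The timing is "taking into account an accrual time of 90 days with 28 days of follow-up", and the result is that "we will need to study 647 patients per intervention group and 647 control patients", with power 0.80 and two-sided alpha 0.05. Allowing for 10% dropout gives 715. This section mentions neither a 15% gain in survival time nor 12% mortality.

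**The concern.** A quantity capped at 28 days cannot rise by 15% when the placebo group already averages close to 28. At 12% mortality most placebo patients contribute the full 28 days, which leaves little room for improvement. The abstract therefore promises power for an effect that no treatment could produce.

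The abstract is where most readers learn what the trial can detect. They would take it as sized for a large gain in survival time. A null result could not be read against such a target. The sample size section does not rescue the figure, because its effect is on another scale and its control group has a very different death rate.

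**Working it through.** **1. Reproducing the plan's 647.** Inputs from the sample size section: hazard ratio 0.85, control median 18 days, accrual A = 90 days, follow-up F = 28 days, power 0.80, two-sided alpha 0.05.

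- Events for a 1:1 comparison (Schoenfeld): 4 × (1.960 + 0.842)² / (ln 0.85)² = 4 × 7.849 / 0.02641 = 1,189.
- Probability of death with exponential survival and uniform accrual: P = 1 − [exp(−λF) − exp(−λ(A+F))] / (λA), with λ = ln 2 / median. For the 18-day median, P = 0.905.
- Ratio taken literally (control relative to intervention): the intervention median is 18 × 0.85 = 15.3 days and P = 0.932. N per group = 1,189 / (0.905 + 0.932) ≈ 647.
- Ratio in the beneficial direction: the intervention median is 18 / 0.85 = 21.2 days and P = 0.871. N per group = 1,189 / (0.905 + 0.871) ≈ 669.

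So 647 rests on the hazard ratio of 0.85 and the 18-day median, with the ratio as literally written.

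**2. Can days alive in 28 rise by 15% at 12% mortality?** The 12% is read as 28-day mortality.

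- Most generous case, every placebo death on day 0: the mean is 0.88 × 28 = 24.64 days. A 15% gain needs 24.64 × 1.15 = 28.34, above 28. The ceiling is 28 / 24.64 − 1 = 13.6%. This bound needs no survival model.
- Constant hazard: λ = −ln(0.88) / 28 = 0.004565 per day, and the mean is 0.12 / λ = 26.28 days. A 15% gain needs 30.23 days. The ceiling is 28 / 26.28 − 1 = 6.5%.
- Weibull hazards with shape 0.5 to 1.5: ceiling 8.8% to 5.2%.
- Read as a proportion surviving: 88% × 1.15 = 101.2%, also impossible.

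**3. Is it the same as a hazard ratio of 0.85?** At 12% placebo mortality:

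- 28-day mortality on treatment: 1 − 0.88^0.85 = 10.3%.
- Mean days alive: 0.10296 / (0.85 × 0.004565) = 26.53, a gain of 0.25 days or 0.9% (0.7% to 1.3% over the Weibull shapes).
- On uncapped exponential time, 0.85 means 1 / 0.85 − 1 = 17.6% longer. A 15% longer time is a hazard ratio of 1 / 1.15 = 0.870, which needs 1,608 events instead of 1,189.

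The two figures agree on none of these scales.

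**4. The two control groups.** A median of 18 days means that at least half of the control patients have died by day 18. Under a constant hazard, 28-day mortality is 1 − 2^(−28/18) = 66%. Conversely, 12% at day 28 implies a median of ln 2 / 0.004565 = 152 days.

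**5. Power if 12% is the rate.** Expected deaths in two groups are n × (0.120 + 0.103), and power is Φ(½√d × 0.1625 − 1.96).

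| n per group | deaths d | power |
|---|---|---|
| 715 | 159 | 18% |
| 647 | 144 | 16% |

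For 80% power: 1,189 / 0.22296 ≈ 5,333 per group. Conversely, solving 4 × 7.849 / (ln HR)² = 715 × (0.12 + 1 − 0.88^HR) gives a hazard ratio of about 0.62, with 141 deaths and mortality of 12% against 7.7%.

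**The case against.** The best defence is that the abstract phrase is loose shorthand for a 15% lower hazard. That is probably what was meant. The analysis is Cox regression, no comparison of mean days alive is planned, and 647 is recovered without the phrase. This limits the damage but does not make the sentence right: it says survival time, and it stands beside the 12% that makes it impossible.

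A second defence is that a median rising from 18 to 18 × 1.15 = 20.7 days fits inside the window. It does, but only with the 18-day median, which the 12% rules out. That median comes from the earlier prophylaxis study, which the Background describes as done in patients with a predicted delirium risk above 50%; the present population has a median risk of about 35%. Different populations may explain the two figures, but one trial cannot be sized on one and described by the other.

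Third, the 12% carries no time point. If it were 90-day mortality, 28-day mortality would be no higher and the ceiling no higher either. A 15% gain needs placebo mortality of at least 1 − 1/1.15 = 13.0% with all deaths on day 0, or about 25% under a constant hazard, and then no deaths at all on treatment.

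Two stronger readings are tempting. A reader might infer that the primary objective is unattainable. It is not, since it asks for the effect on 28-day survival without a threshold. A reader might also infer from the literal ratio that the trial was planned to show harm. The Background cites a hazard of 0.8 for 28-day mortality with haloperidol, so the intended direction is benefit; the wording and the N that follows from it are what need correcting.

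**Conclusion.** The point holds for the stated detectable effect, and only for that. At 12% placebo mortality a 15% gain in days alive within 28 cannot occur whatever the timing of deaths: the ceiling is 13.6%, and 6.5% under a constant hazard. The figure is also not the planned effect, which is a hazard ratio of 0.85 on an 18-day control median.

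The underlying fault is that the article uses two incompatible control groups, one with 12% mortality and one with about 66%. It would be wrong to say that the sample size section itself planned for 12.0% against 10.3%; that pair arises only when the abstract's 12% is combined with the ratio of 0.85. On the 18-day median, 0.85 in the beneficial direction is roughly 66% against 60%.

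Assumptions: the 12% is 28-day mortality. The 66%, 6.5%, 0.25-day and sample size figures assume a constant hazard; the 13.6% ceiling does not. The 10.3% and the power figures assume proportional hazards, and the power figures also assume that every patient is followed to day 28.

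**What to change.** In both the abstract and the sample size section, state the target as a hazard ratio for death of 0.85, haloperidol relative to placebo. Give the matching 28-day mortality in each group, from a single control event rate used in both places, and drop the 15% gain in survival time.

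If the rate is 12%, the effect reads 12.0% against 10.3%, about 0.25 days or 0.9%. Replacing the phrase alone would then be worse than leaving it, because the sentence would claim 80% power for that difference. Either restate power as about 18% at 715 per group (16% at 647), or give the hazard ratio that 715 per group can detect with 80% power, about 0.62 on the calculation above.

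If the sample size section keeps its own inputs, reversing the ratio changes its result from 647 to about 669 per group before dropout, so that figure and those that follow from it must be restated as well.

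The cost is more than wording: the stated target and the stated power both become less favourable. The primary objective need not change.

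### The Abstract claims 80% power in both haloperidol groups, but under the fixed sequence the 1 mg comparison has about 69% power if both doses share the planned hazard ratio of 0.85

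*Protocol article*

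**What the plan says.** The Methods paragraph of the Abstract gives a total of 2,145 randomised patients, 715 per group, "with a power of 80% and alpha of 0.05 in both intervention groups".

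The section on sample size calculation and statistics gives the derivation. Its inputs are a control group in which "the median survival time in the control group was 18 days", and one effect size that is not dose-specific: "If the true hazard ratio of control patients relative to intervention patients is 0.85". With 90 days of accrual and 28 days of follow-up it arrives at 647 patients in each intervention group and 647 controls, "to be able to reject the null hypothesis that the experimental and control survival curves are equal with probability (power) 0.80". It adds: "The Type I error probability associated with this null hypothesis test is 0.05". Dropout of 10% takes this to 715 per group.

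The same section then fixes the order of testing: "A fixed sequence procedure will be followed". The 2 mg dose is compared with placebo first, at two-sided alpha 0.05. Only after that null hypothesis is rejected will "subsequently the lower dosage of prophylactic haloperidol will be compared with placebo". Neither the power nor the sample size is adjusted for this condition.

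**The concern.** A fixed sequence lets each test use the full alpha. The cost is power for the second test, because that test is not carried out when the first one fails. The calculation treats one pairwise comparison in isolation, while the Abstract attaches its 80% to both active groups. If the first comparison fails in a fifth of trials, the second can keep 80% only if it succeeds in every remaining trial, and nothing in the plan assumes that.

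At stake is how a negative or untested 1 mg result will be read. A reader who believes that the 1 mg comparison had 80% power will take the lack of a positive finding as stronger evidence against that dose than the design supports.

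**Working it through.** **Inputs from the sample size section:** control median 18 days; hazard ratio 0.85, the same for either dose; accrual 90 days; follow-up 28 days; two-sided alpha 0.05; power 0.80; 647 evaluable per arm; one placebo arm shared by both comparisons; 1 mg tested only after 2 mg is significant.

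**Step 1: reproduce the 647.**
- Schoenfeld events for one comparison: 4 × (1.960 + 0.842)² / (ln 0.85)² = 4 × 7.849 / 0.02641 = 1,189.
- Exponential survival with uniform accrual, control hazard ln 2 / 18 = 0.0385 per day. With the hazard ratio read as worded (control relative to intervention), the event probabilities are 0.905 (control) and 0.932 (intervention).
- Patients per arm: 1,189 / (0.905 + 0.932) = 647.2. Power at 647 is 0.800.

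The stated figure is thus reproduced as 80% power for one dose against placebo.

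**Step 2: correlation of the two tests.** Each statistic contrasts an active arm with the same placebo arm. With equal arms, half of each statistic's variance comes from placebo, so the correlation is 0.5. The article does not state this; it follows from the design.

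**Step 3: power under the sequence.** Each statistic has mean 1.960 + 0.842 = 2.802 under the planned effect. In the final analysis 1 mg succeeds only if both exceed 1.960:

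P(Z(2 mg) > 1.960 and Z(1 mg) > 1.960), bivariate normal, correlation 0.5 = **0.687**.

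A simulation of 200,000 draws gave 0.688. This is the power for 1 mg and also the power to show both doses superior. Given success of 2 mg, the power for 1 mg is 0.687 / 0.80 = 0.859.

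**Step 4: sensitivity.** For other hazard ratios each mean is scaled as 2.802 × ln(HR) / ln(0.85).

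| Case | Power, 2 mg | Power, 1 mg under the sequence |
|---|---|---|
| Both 0.85 (plan) | 80% | 68.7% |
| Both 0.85, final alpha 0.049 | 79.8% | 68.4% |
| Both 0.85, tests independent | 80% | 64.0% |
| Hazard on haloperidol reduced to 0.85 (event probabilities 0.905 and 0.871), 647 per arm | 78.7% | 66.9% |
| 2 mg 0.82, 1 mg 0.85 | 92.8% | 76.8% |
| 2 mg 0.80, 1 mg 0.85 | 97.0% | 78.9% |
| 2 mg 0.78, 1 mg 0.85 | 99.0% | 79.7% |
| 2 mg 0.85, 1 mg 0.90 | 80% | 40.8% |

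The unequal hazard ratios are illustrative assumptions; the plan gives none.

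**The case against.** The strongest defence is that the Abstract is condensed and means only that each active arm is sized at 80% against placebo. Pairwise power is commonly reported for multi-arm trials, the 647 is correct for that purpose, and the sequence is disclosed in the body. It stands that there is no slip in the 647 itself. But the pairwise reading does not rescue the claim for 1 mg, because the final analysis allows no test of 1 mg that is not conditional on 2 mg.

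A second defence is that 2 mg may work better. The Background adds the third arm because a higher dose might reduce delirium further, and the study used for sizing gave 1 mg three times daily. With 1 mg held at 0.85 and a stronger 2 mg effect, the shortfall shrinks to between about 3 points and less than 1. This stands as a limit on the 69%, but the sample size section assumes no such difference.

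Third, the superiority look after 1,000 patients covers either dose at P < 0.003 with no stated order. If a win for 1 mg there counts, simulation puts the gain at about one point (68.4% to 69.6%).

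A reader might go further and infer that the rationale for the third arm makes power for 1 mg lower still. The documents do not support this as a general statement. Power falls if 2 mg is fixed at 0.85 and 1 mg is weaker, and rises if 1 mg is fixed at 0.85 and 2 mg is stronger. A reader might also bring in the 12% placebo mortality in the Abstract, which would pull every power figure far down. That conflicts with the 18-day median and is a separate matter; it adds no weight here.

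**Conclusion.** Wrong as written. On the sample size section's own assumptions, 80% is the power for 2 mg against placebo only. For 1 mg under the fixed sequence, and for showing both doses superior, it is about 69%, an overstatement of about 11 points. This rests on a common hazard ratio of 0.85, equal arms, a shared placebo group and the 18-day control median. With unequal effects the figure could lie close to 80% or far below 69%.

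The point concerns the power statement alone. A reader might infer that the testing procedure is invalid, but a fixed sequence controls the type I error across the two final comparisons.

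**What to change.** In the Abstract, delete the phrase that attaches the 80% to both intervention groups. In the Abstract and the sample size section, state the two figures separately on the section's assumptions: 80% for 2 mg versus placebo, and about 69% for 1 mg versus placebo under the fixed sequence if both hazard ratios are 0.85. One sentence should say that the second figure depends on the effect of both doses.

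The cost is a few words in two places. Sample size, testing order and analysis stay as they are. For scale, keeping 80% for both doses would need about 88% power per comparison, or about 807 evaluable patients per arm (647 × 1.247) instead of 647. Correcting the statement is the proportionate course.

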**Discussion:**

This will be the first large-scale multicenter randomized controlled prevention study with haloperidol in ICU patients with a high risk of delirium, adequately powered to demonstrate an effect on 28-day survival.

**Trial registration:**

Clinicaltrials.gov: NCT01785290.

EudraCT number: 2012-004012-66.

## Background

Delirium is a neuropsychiatric disorder characterized by an acute onset of confusion, inattention, and a change in level of consciousness that tends to fluctuate during the day [1,2]. The incidence of delirium in intensive care unit (ICU) patients is high [3-6], approximately 30–50%. Further, its occurrence is associated with detrimental outcome, including prolonged duration of mechanical ventilation, increased ICU and hospital length of stay (LOS) [4-6], unplanned removal of tubes and catheters [6], increased mortality [6-8], and long-term cognitive disturbances [9,10]. Therefore, a strategy that can prevent delirium in high-risk patients may also decrease short-term (i.e., 28-day) mortality.

The first step in the management of delirium is to treat the underlying disease. If delirium does not subside, haloperidol is the most frequently used pharmacologic treatment of delirium. However, this drug may also be used to prevent delirium. In non-ICU patients, beneficial effects have been reported of prophylactic haloperidol in older and surgical patients [11,12]. For critically ill patients, data concerning prevention with anti-psychotic drugs are scarce and inconsistent [13-15]. In one retrospective cohort study, ICU patients who received haloperidol were found to have a lower mortality rate compared to ICU patients that did not receive haloperidol [16]. Only one prospective, randomized trial in critically ill patients is available, showing that haloperidol prophylaxis in non-cardiac surgical ICU patients had beneficial effects on delirium incidence and the number of delirium free-days [17]. However, only a very low dose, for 12 h infusion of haloperidol was administered and many of the patients were in the ICU for less than 24 h [17]. Thus, there are no large, definitive trials that have studied the effect of haloperidol prophylaxis in ICU patients.

Recently, a model was developed and validated to predict delirium in ICU patients [18]. With this model, the effectiveness of preventive strategies can be compared in different groups that differ in *a priori* risk of delirium. This delirium prediction model was used to identify high-risk ICU patients (i.e., *a priori* risk of delirium >50%). Compared to a historical control group, prophylactic low-dose haloperidol was associated with better delirium related outcomes. In this high-risk group (>50%) of critically ill patients, incidence of delirium was significantly lower in the preventive treatment group (65%), compared to the control group (75%). Furthermore, haloperidol prophylaxis was associated with a hazard rate of 0.8 for 28-day mortality [19]. However, because of the pre-/post-implementation design of this trial, other factors that may have changed between the study periods may have influenced these findings. Nevertheless, the results suggest that prevention of delirium might be beneficial in critically ill patients. Since no relevant side effects associated with the administration of a low dosage of haloperidol were reported in the prophylactic studies [11,12,17,19], it is conceivable that a higher dose of haloperidol may exert more pronounced beneficial effects. Furthermore, the optimal dosage of haloperidol in critically ill patients, as well as the occupancy levels of dopamine-2 receptors and sigma-1 receptors when administering haloperidol, remain unknown. Therefore, in the present study proposal the effects of two dosages of haloperidol versus placebo will be determined.

Given the fact that the development of delirium can be predicted only 24 h after ICU admission, and the clear relation between time to treatment with haloperidol and the duration of delirium [19], initiation of prophylaxis as early as possible is warranted. Based on our historical data, the median predicted risk of delirium is approximately 35% in patients with an expected stay on the ICU of over one day; this is considered a high risk for delirium development. A clinical estimation of an ICU LOS >1 day is possible within the first few hours after ICU admission. Previous studies that included patients using similar criterion of an expected ICU LOS were found feasible [20,21]. Therefore, the clinical estimation by the attending ICU-physician of an ICU LOS >1 day will be used as an inclusion criterion for this study, in which the prediction to develop delirium (using the PRE-DELIRIC model [18]) will be used to facilitate post-hoc analyses to investigate which patients benefit most from prophylactic therapy. By using the PRE-DELIRIC score as an *a priori* determined post-hoc analysis, we will learn if the putative beneficial effect of haloperidol is related to the risk to develop delirium, or comparable in all patients, independent of the baseline risk to develop delirium. In addition, it will facilitate the determination of a cut-off level for the PRE-DELIRIC score.

Potential side effects of haloperidol include extra pyramidal symptoms, drowsiness, agitation, and ventricular arrhythmias. The latter are extremely rare (only case-reports are published [22-25]) and dose dependent. With the haloperidol dosage that will be used in the present study (3x1 mg or 3x2 mg intravenously daily), no relevant side effects are expected, regardless of underlying condition, organ dysfunction, and concomitant medication. Nevertheless, and given the preventive nature of this study, extra attention is being paid to the recognition of possible side effects of haloperidol that could mitigate its potential beneficial effects. Importantly, in three recent prophylactic haloperidol studies [11,17,19] no relevant side effects, and in particular no ventricular arrhythmias, were reported using similar low dosages of haloperidol as described in the present protocol. Regarding the choice of haloperidol dosage, this was based on the previous study in which no relevant side effects were found when using a prophylactic dose of 3x1 mg in delirium high-risk ICU patients, and resulted in a significant decrease of delirium incidence [19]. However, in this high-risk group (mean delirium risk of 75%) the incidence was still 65%, suggesting that a higher dosage of haloperidol might decrease the incidence of delirium to a greater extent. For this reason, and taking into account the non-relevant side effects, we choose to add a third arm using a higher dose of 3x2 mg haloperidol.

The aim of this study is firstly to determine the effect of two different low dosages of prophylactic haloperidol on 28-day mortality as well as the incidence of delirium and other delirium related outcome measures and quality of life, compared with placebo, in ICU patients with an expected ICU stay of >1 day. Secondly, to relate the potential beneficial effects of haloperidol to the *a priori* risk of developing delirium, using the PRE-DELIRIC model [18]. Lastly, to evaluate possible side effects of prophylactic haloperidol.

